Perhaps the best stroke rehabilitation program should combine rehabilitation therapies with definite efficacy on motor function that act on different aspects of motor relearning principles to maximize motor function improvement in stroke survivors [21–23]. It has been proposed that when muscles are activated by electric stimulation and other forms of physical exercise (i.e., RAT, task-oriented training) make voluntary efforts or provide the major interaction effect, a synergistic-enhanced rehabilitation effect may be produced [7, 21]. From this perspective, synergy-based FES combined with RAT may be a novel and more effective therapy for upper limb function enhancement in stroke survivors. However, to our knowledge, few studies have examined the effectiveness and safety of combined synergy-based FES and RAT for upper limb function improvement in stroke patients, especially for motor control in RTG movements. Therefore, the present protocol was designed for an assessor-blinded randomized controlled trial, which will include 3 groups: the FES + CRP group, RAT + CRP group and FES-RAT + CRP group. The purposes of this protocol are as follows:

### Aim 1

To provide high-quality evidence of synergy-based FES for improvement of the upper limb function after stroke.

### Aim 2

To examine the effectiveness and safety of combined synergy-based FES and RAT for upper limb function improvement after stroke.

### Aim 3

To compare the efficacy differences in upper limb function improvement after stroke between the FES-RAT therapy and FES or RAT groups.

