### Sample size calculation

The G*power software was utilized to determine the minimum sample size required to detect a significant between-group difference in the present research [24]. In a study of RAT for upper-extremity poststroke rehabilitation, Takebayashi et al. [25] used the minimal clinically significant difference as a reference (4.25 points), the mean difference in the FMA-UE score between patients in the RAT and CRP was 4.50 points and standard deviations between patients were 6. Based on a prior two-way repeated analysis of variance (ANOVA) F test, with a power of 0.80, an effect size of 0.158, three groups, five measurements, correlation among repeated measures of 0.5, and an alpha level of 0.05, 129 participants were required for this study. To account for a conservative drop-out rate of 20%, the final sample size will therefore be 54 participants in each group, for a total of 162 participants.

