### Statistical analysis

All statistical analyses will be performed with IBM SPSS (IBM Corp. Released 2013. IBM SPSS Statistics for Windows, Version 22.0. Armonk, NY: IBM Corp.) by statisticians who are blinded to the group allocation. The analyses will be performed on an intention-to-treat basis. The Shapiro–Wilk (SW) test will be used to examine the normal distribution of the continuous variables comprising demographic and outcome measures. Continuous variables will be described as the mean ± SD for those with normal distributions or the median for those with nonnormal distributions, and categorical variables will be described as the frequency. The χ^2^ test or Fisher’s exact test will be used to examine the comparisons among the three groups for categorical variables. When the normality of data distribution is determined, two-way of variance with repeated measures will be applied to examine the main effects of the group and time factors, as well as the group-time interaction effects. A simple effect post hoc analysis will be conducted when the time-group interaction is significant. Furthermore, the linear mixed model will be adjusted for age, sex and type of stroke if homogeneity is not found. The significance level for all statistical tests will be set at 0.05, corrected for multiple comparisons using the Bonferroni-adjusted method and accompanied by a 95% confidence interval.

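### The Aim 3 contrasts (FES-RAT versus FES, FES-RAT versus RAT) are planned only behind a significant 8-df group-by-time interaction, so the trial's central comparison may get no planned test or estimate

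*Protocol article*

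**What the plan says.** Aim 3, at the end of the Background, is "To compare the efficacy differences in upper limb function improvement after stroke between the FES-RAT therapy and FES or RAT groups". That is two specific between-arm contrasts: the combination against each of its components.

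Under Statistical analysis, a two-way repeated-measures ANOVA examines "the main effects of the group and time factors, as well as the group-time interaction effects". The pairwise step comes next and is conditional: "A simple effect post hoc analysis will be conducted when the time-group interaction is significant". The section closes with a general rule: "The significance level for all statistical tests will be set at 0.05, corrected for multiple comparisons using the Bonferroni-adjusted method". It adds that 95% confidence intervals will accompany the tests. The number of comparisons in the Bonferroni family is not given.

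A linear mixed model adjusted for age, sex and stroke type is a fallback if homogeneity fails. No pairwise contrast is attached to it, and none is attached to a significant group main effect.

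**The concern.** With three arms and five visits the interaction has (3−1)×(5−1) = 8 degrees of freedom. It responds to any departure from parallel profiles over all visits, so it is a diffuse test of a focused question. An advantage present at the end of treatment can be diluted across the other visits, especially if it fades during follow-up.

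If the interaction is not significant, the plan contains nothing that answers Aim 3. The group main effect does not replace it. It is a 2-df test that cannot say which arm differs, and it averages in the baseline visit, where randomised arms should not differ.

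Two things are at stake. The central comparison may get no planned answer, although a small or null difference with its interval would itself be informative in a comparison of active treatments. And contrasts reported only after the interaction has passed are selected on significance, so their estimates and intervals are no longer unconditional.

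**Working it through.** **Inputs from Sample size calculation.** The article assumes "correlation among repeated measures of 0.5, and an alpha level of 0.05, 129 participants were required for this study". Its effect size f is 0.158 and its target power 80%, for three arms and five visits. The planning difference is described as "the mean difference in the FMA-UE score between patients in the RAT and CRP was 4.50 points and standard deviations between patients were 6", with 4.25 points as the minimal clinically significant difference. So SD = 6, ρ = 0.5, N = 129 (43 per arm), and 129/0.80 = 161.25, rounded up to 162 (54 per arm).

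**The plan's own figure.** For the interaction, the usual repeated-measures formula is λ = f²·N·m/(1−ρ). With f = 0.158 this gives 0.02496 × 129 × 5/0.5 = 32.2 and power of about 99%; 63 participants would suffice for 80%. The between-groups test would need 235. The stated 129 does not follow from either. That is a separate matter; 129 is used here only for the 43 per arm.

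**Assumptions of mine.** FES = RAT. FES-RAT is better by D at 12 weeks (T3). The fraction of D present at T1–T5 is either sustained (0, 0.5, 1, 1, 1) or fading (0, 0.5, 1, 0.5, 0.25). The Bonferroni family is three pairwise tests (0.05/3). D = 3 stands for a smaller effect.

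**Step 1: does the interaction pass?** With one arm differing, the mean squared group deviation is (4/9 + 1/9 + 1/9)/3 = 2/9. The mean squared time deviation is 0.16 (sustained) or 0.11 (fading). So f = (D/6)·√(2/9 × 0.16) or (D/6)·√(2/9 × 0.11).

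For D = 4.50, f = 0.141 or 0.117, and λ = f² × 129 × 5/0.5 = 25.8 or 17.7. Against the 5% critical value of F(8, 504), 1.957, power is 97% or 87%. The same steps give 95% or 82% at 4.25 points and 65% or 46% at 3 points. Simulation agrees to within about half a percentage point.

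**Step 2: what does the gate cost?** 20,000 simulated trials per row, compound symmetry, unadjusted T3 contrasts, both required in favour of FES-RAT at 0.05/3:

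| D, pattern | Interaction not significant | Both, no gate | Both, behind gate | Cost of gate (points) |
|---|---|---|---|---|
| 4.50 sustained | 3% | 75.9% | 74.0% | 1.9 |
| 4.50 fading | 13% | 76.3% | 69.5% | 6.8 |
| 4.25 sustained | 5% | 69.1% | 66.5% | 2.6 |
| 4.25 fading | 18% | 69.2% | 60.6% | 8.6 |
| 3 sustained | 35% | 29.6% | 21.6% | 8.0 |
| 3 fading | 53% | 29.5% | 19.3% | 10.2 |

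With all 54 per arm observed, the interaction misses in about 1–6% of trials at 4.50 points and 23–43% at 3 points.

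**Step 3: keep the components apart.** At 4.25 points, fading, power for both contrasts is 94% with baseline adjustment at 0.05; 84% unadjusted at 0.05; 69% unadjusted at 0.05/3; and 61% with the gate added. Dropping baseline adjustment costs about 10 points, Bonferroni for three about 15, and the gate about 8.

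**Step 4: how often would the gate hide a clear answer?** Both baseline-adjusted T3 contrasts are significant at 0.05 while the interaction is not in about 4% (sustained) or 14% (fading) of trials at 4.25 points, and in 16% or 25% at 3 points.

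**The case against.** The best defence is that the text does not say pairwise tests are run only after a significant interaction, that the group main effect is tested without any gate, and that confidence intervals are promised. A fuller analysis plan may also add contrasts. This does not remove the point: the condition is stated, no other pairwise step is named, and the main effect cannot identify which arm differs.

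The case against a large effect is stronger, and most of it stands. A reader might infer that the rule cuts power sharply. At the article's planning difference of 4.50 points the interaction passes in 87–97% of trials, and the gate costs about 2–7 points. The heavy loss needs a smaller effect. Smaller effects are plausible, because 4.50 points is RAT against conventional rehabilitation while Aim 3 compares active arms, but 3 points appears nowhere in the article.

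A reader might also blame the gate for the whole distance from 94% to 61%. Most of it comes from Bonferroni and from the lack of baseline adjustment, which are separate choices.

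Nor is "corrected for multiple comparisons using the Bonferroni-adjusted method" an error in itself. Correcting three pairwise tests in a three-arm trial is ordinary conservative practice. The family of three is my inference, and FES versus RAT is not irrelevant: Aim 1 concerns FES, and there is no arm with conventional rehabilitation alone.

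Finally, T3 is my choice. The article names no primary visit, and it treats the 6-month follow-up as part of the design.

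**Conclusion.** The point holds as a defect in how the analysis is ordered. Followed as written, the plan can leave Aim 3 with no planned test or estimate. The chance is small near the planning difference and roughly one in three to one in two if the true advantage is nearer 3 points.

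The documents do not support calling this a general collapse of power, or calling the Bonferroni correction wrong. The figures rest on equal FES and RAT means, compound symmetry, the two assumed time patterns, a Bonferroni family of three and T3 as the visit of interest. The existence of the gate rests on none of these. The trial is not invalidated, but its central comparison is made conditional for no gain. This is a cheap improvement, best made before unblinded analysis.

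**What to change.** Replace the conditional sentence with a prespecified one. The primary contrasts are FES-RAT minus FES and FES-RAT minus RAT on FMA-UE at one named visit (for example T3, end of treatment), adjusted for baseline FMA-UE. Both are tested and reported with 95% confidence intervals whatever the interaction result.

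Match the multiplicity rule to the claim and state the family. If FES-RAT must beat both components, require both at two-sided 0.05 with no further adjustment. If either contrast alone may support a claim, use Holm or 0.025 each. Report the interaction, FES versus RAT and the other visits as secondary.

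The cost is a few sentences and no new data. The price is that one visit must be named in advance, and that FES versus RAT and the remaining visits become secondary.

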**Methods:**

This will be an assessor-blinded randomized controlled trial involving a 12-week intervention and a 6-month follow-up. Stratified randomization will be used to equally and randomly assign 162 stroke patients into the FES + conventional rehabilitation program (CRP) group, RAT + CRP group and FES-RAT + CRP group. Interventions will be provided in 5 sessions per week, with a total of 60 sessions. The primary outcome measurements will include the Fugl-Meyer Assessment and Biomechanical Assessment of RTG movements. The secondary outcome measurements will include quality of life and brain neuroplasticity assessments by MRI. Evaluations will be performed at five time points, including at baseline, 6 weeks and 12 weeks from the start of treatment, and 3 months and 6 months following the end of treatment. A two-way analysis of variance with repeated measures will be applied to examine the main effects of the group, the time factor and group-time interaction effects.

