### Randomization, allocation concealment and blinding

To minimize any potential bias, the eligible participants will be randomly assigned to 3 groups using stratified randomization with sex (male/female), stroke type (hemorrhage/infarction) and dominant hand (left/right) as factors [27]. After categorization, there will be eight subgroups: (1) male, hemorrhage, left hand dominant; (2) male, hemorrhage, right hand dominant; (3) male, infarction, left hand dominant; (4) male, infarction, right hand dominant; (5) female, hemorrhage, left hand dominant; (6) female, hemorrhage, right hand dominant; (7) female, infarction, left hand dominant; (8) female, infarction, right hand dominant. For any one subgroup, the participants will be randomly divided into groups A, B, and C; then, all A, B, and C groups will be merged to form new group A, B, and C groups. The randomization number lists will be generated by the random number generator of SPSS software (IBM Corp. Released 2013. IBM SPSS Statistics for Windows, Version 22.0. Armonk, NY: IBM Corp.).

The allocation of participants will be secured in opaque numbered and sequentially sealed envelopes, which will be prepared by an independent researcher. The corresponding envelopes will be opened to ascertain a patient’s group assignment after all baseline assessments have been completed by the participants. In addition, physiotherapists with the same level, robotic and FES operators will also follow randomization and be randomly assigned to one of the groups.

The outcome assessors and statisticians who implement the final statistical analyses will be blinded to avoid any potential detection bias.

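### Baseline is one of five levels in a covariate-free ANOVA, which dilutes the group main effect, and covariate adjustment hangs on an undefined homogeneity check

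*Protocol article*

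**What the plan says.** All places are in the Protocol article.

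- **Statistical analysis.** If the data are normal, a two-way repeated-measures ANOVA "will be applied to examine the main effects of the group and time factors, as well as the group-time interaction effects". No covariate is listed. Simple effects follow only when the interaction is significant. None of the three effects is named as the primary test.
- **Statistical analysis, adjustment.** "the linear mixed model will be adjusted for age, sex and type of stroke if homogeneity is not found". The section does not say whether this means homogeneity of baseline characteristics, of variances or of something else, nor how it is judged.
- **Time levels.** The abstract states: "Evaluations will be performed at five time points, including at baseline". Outcome measurements labels baseline T1, and Sample size calculation uses "three groups, five measurements, correlation among repeated measures of 0.5". The Statistical analysis section does not itself list the levels, but these three places together make T1 one of the five.
- **Randomization, allocation concealment and blinding.** Allocation is by "stratified randomization with sex (male/female), stroke type (hemorrhage/infarction) and dominant hand (left/right) as factors". Envelopes are opened only after all baseline assessments are complete.

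**The concern.** T1 precedes allocation, so the expected difference between groups there is zero. A group main effect taken over five levels averages that zero with four post-baseline visits, and so understates the treatment effect. Using T1 as a response level also means that it is not used as a covariate, although it is measured on everyone and, at the plan's correlation of 0.5, would explain 0.5² = 25% of the variance of any later visit.

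The default model also leaves out the factors that governed the randomisation, so any outcome variation they explain stays in the error term and standard errors are larger than they need be. Finally, whether sex, stroke type and age are adjusted for depends on the result of an undefined check. The model that produces the reported estimate is thus chosen after the data are seen, by a rule that two analysts could apply differently.

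At stake are power, the size of the reported main effect and pre-specification. The comparison stays randomised under either model.

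**Working it through.** **Inputs.** Sample size calculation gives correlation ρ = 0.5, five measurements, three groups, reference difference 4.50 points, SD 6, f = 0.158, N = 129 evaluable and 162 recruited. My assumptions are compound symmetry, zero expected difference at T1 and a constant effect δ at T2–T5.

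**The plan's own figure.** With "with a power of 0.80, an effect size of 0.158" and the other stated inputs, noncentral-F calculations give N = 237 for the group effect, 63 for the interaction and 51 for time. The stated 129 matches none of these. That is a separate matter. Here it means only that the plan's N does not show which effect was meant to be primary. The dropout step is right: 129/0.8 = 161.25, rounded up to 162.

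**Dilution of the group main effect.** (0 + 4δ)/5 = 0.8δ. With δ = 4.50 this is 3.60 points.

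**Variances per patient, in units of SD² (multiplied by 36 in brackets), at ρ = 0.5.**

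- Five-visit mean: (1 + 4ρ)/5 = 0.60 (21.6)
- Mean of T2–T5: (1 + 3ρ)/4 = 0.625 (22.5)
- Mean of T2–T5 adjusted for baseline: (1 + 3ρ)/4 − ρ² = 0.375 (13.5)
- Mean of T2–T5 minus T1: (1 + 3ρ)/4 + 1 − 2ρ = 0.625 (22.5)

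**Information = (share of δ estimated)² / variance.**

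| ρ | Five-level main effect | Baseline-adjusted T2–T5 mean | Ratio |
|---|---|---|---|
| 0.3 | 0.64/0.44 = 1.45 | 1/0.385 = 2.60 | 1.8 |
| 0.5 | 0.64/0.60 = 1.07 | 1/0.375 = 2.67 | 2.5 |
| 0.7 | 0.64/0.76 = 0.84 | 1/0.285 = 3.51 | 4.2 |

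**Power of the 2-df group test**, treating f = 0.158 as the post-baseline effect, ρ = 0.5, noncentrality N·f²·information:

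| N | Five levels | T2–T5, unadjusted | T2–T5, baseline-adjusted |
|---|---|---|---|
| 129 | 0.36 | 0.51 | 0.74 |
| 162 | 0.44 | 0.61 | 0.84 |

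The N for 80% power is 366, 246 and 150 respectively.

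**Tests that are not diluted.**

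- Interaction: under a constant post-baseline effect its noncentrality is N·f²·1.6, since 1/0.625 = 1.6, spread over 8 df. With f = 0.158, power is 0.30 at N = 129 and 0.38 at N = 162. With group means evenly spaced over 4.50 points, f = √[(2.25² + 0 + 2.25²)/3]/6 = 0.306 and power is 0.90 and 0.96.
- Change contrast (T2–T5 mean minus T1) against the adjusted mean, variance ratio: 0.625/0.375 = 1.67 at ρ = 0.5, 0.875/0.385 = 2.3 at ρ = 0.3, 0.375/0.285 = 1.3 at ρ = 0.7.
- Simple effect at one visit: 1/(1 − ρ²) = 1/0.75 = 1.33 times the baseline-adjusted variance at ρ = 0.5.

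**Factors, side by side.**

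| Factor | Stratifies randomisation | Default ANOVA | Conditional model |
|---|---|---|---|
| Sex | yes | no | yes |
| Stroke type | yes | no | yes |
| Dominant hand | yes | no | no |
| Age | no | no | yes |
| Baseline FMA-UE as covariate | no | no | no |

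**The case against.** The best defence is that the group main effect is only one of three planned tests. The interaction takes T1 as the reference for change, and the simple effects are read visit by visit, so neither is averaged with baseline. Using T1 as a response is a valid choice, only less efficient. Sex and stroke type do appear in the conditional model. Larger standard errors are conservative. An article may leave model detail to an analysis plan.

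Most of this stands and sets the limits of the point:

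- A reader might infer that every planned treatment comparison is diluted by a fifth. The documents do not support that: the 0.8 factor belongs to the group main effect alone.
- A reader might take 2.5 as the gain from baseline adjustment in general. It compares the five-level main effect with an adjusted T2–T5 mean. Against the change contrast the ratio is 1.67, and at a single visit against the planned simple effect it is 1.33. The protocol names no single visit as primary.
- A reader might say that stratification is ignored altogether. That is true of the default model, but the conditional model holds two of the three factors. The documents give no figures from which to size the loss from omitting them.

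The interaction does not fully rescue the plan. It is not named as primary, its 8 df cost power when the effect is small and constant, and simple effects are reached only through its significance. Nor does leaving detail to an analysis plan answer the point, because the article states the covariates and the condition for using them.

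**Conclusion.** The point holds as one of efficiency and pre-specification and should be corrected, but it does not undermine validity. The five-level group main effect estimates 0.8 of a constant post-baseline effect and carries 1/2.5 of the information of a baseline-adjusted T2–T5 mean at ρ = 0.5 (1/1.8 to 1/4.2 for ρ from 0.3 to 0.7). The undiluted tests lose precision only through the missing baseline adjustment. These sizes rest on compound symmetry and on an effect fully present by T2, halfway through treatment; an effect that builds up or fades would change them. The faults of wording need no such assumption: the trigger for adjustment is undefined and data-dependent, baseline FMA-UE is never a covariate, and dominant hand is in neither model.

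**What to change.** Make the main analysis a linear mixed model with T2–T5 as outcomes. Include as fixed covariates the baseline value of the outcome (by visit), sex, stroke type and dominant hand, with age optional. Include them always, whatever any homogeneity or balance test shows, and delete the conditional clause. Have the sponsor name in advance the post-baseline contrast that gives the treatment effect, either a stated visit or the T2–T5 average, and do not read it from the five-level group main effect.

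The cost is analysis wording only. Baseline outcomes and demographics are collected at T1, and the stratification factors are needed to randomise.

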### Ethics and dissemination

This study procedure will be conducted in accordance with the principles of the Declaration of Helsinki in its current version (for details, see www.wma.net). Ethics approval (2023-7th-HIRB-034) was granted by the Research Ethics Committee of the Ethics Committee of the Seventh People's Hospital of Shanghai University of Traditional Chinese Medicine. The results of the study will be published in peer-reviewed scientific journals and presented at conferences and workshops after study completion.

